#### 2.4.3. MRI Data Acquisition

An MRI scan will be carried out using a 3.0TGE Signa MR750 system (GE Healthcare, Milwaukee, USA) in the Hospital of Chengdu University of TCM. High-resolution 3D T1-weighted anatomical images using a 3D spoiled gradient-recalled sequence will be produced. The acquisition parameters are as follows: repetition time (TR)/echo time (TE) = 5.97/1.96 ms, field of view (FOV) = 240 × 240 mm^2^, flip angle = 12°, matrix size = 512 × 512, 156 slices, and voxel size = 1 × 1 × 1 mm^3^.

Resting-state fMRI images will be obtained using a gradient-recalled echo planar imaging sequence with the following parameters: TR/TE = 2000/30 ms, FOV = 220 × 220 mm^2^, flip angle = 90°, matrix size = 64 × 64, 43 transverse slices without slice gap, voxel size = 3.75 × 3.75 × 3.2 mm^3^, and a total of 266 volumes for each subject.

MRI will be performed during the periovulatory phase (days 12–16 of the menstrual cycle) [47, 48]. All participants will be free from a typical migraine attack for, at least, 1 week prior to the MRI scan [47]. During the examination, subjects will be instructed to lie down with their eyes closed, not to think of anything, and particularly not to fall asleep. Foam padding will be used to restrict head motion, and earplugs will be used to attenuate scanner noise.

### 2.5. Sample Size, Randomization, and Blinding

#### 2.5.1. Sample Size Calculation

Following a previous study, we anticipate that the change in the average number of migraine days in the acupuncture group will be 4.1 ± 3.5, and in the flunarizine group, it will be 1.9 ± 2.3 [37]. Assuming that *α* = 0.05 and 1 − *β* = 0.80, 30 patients will be required for each group, as calculated using *G*^*∗*^Power V3.1.9.2 software. There is no consensus on sample size for neuroimaging and gut microbiota research. A review of previous similar studies suggests that 12–27 individuals in each group is a reasonable sample size for stable and reliable results [49, 50]. Finally, a total of 66 patients will be recruited to compensate for a withdrawal rate of 10%.

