**Methods:**

This randomized clinical trial will recruit 66 patients with migraine without aura. Participants will be randomly assigned in a 1 : 1 ratio to an acupuncture group or a control group. The acupuncture treatment strategy is based on experience from our previous study and consensus meetings with clinical experts. Patients will receive 12 sessions of manual acupuncture treatment (once every other day to a total of three times per week, followed by a 2-day break). Flunarizine will be administered at a dose of 5 mg daily in the control group. Participants in both groups will receive treatment for a period of 4 weeks. The primary outcome is the change in frequency of migraine attacks, and the secondary outcomes include the changes in migraine days (days on which migraine attacks occurred), average migraine severity, gastrointestinal symptoms, psychiatric symptoms, and quality of life. Fresh stool samples will be collected, and 16S ribosomal RNA gene sequencing analysis will be used for gut microbiota. Magnetic resonance imaging will be applied to detect between-group changes in brain function. The abovementioned indicators will be collected at baseline, after a 4-week intervention, and at the 12-week follow-up. *Discussions.* From the perspective of brain-gut regulatory mechanisms, we will combine brain neuroimaging and gut microbiological data to partially reveal the similarities and differences of acupuncture and flunarizine on the treatment of migraine. The trial is registered with ChiCTR2000034417.

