### 2.2. Trial Design

Study participants will be patients who have migraine without aura (MwoA). A total of 66 patients meeting the diagnostic criteria of the International Classification of Headache Disorders [40] will be recruited and randomly assigned to two groups (1 : 1 allocation ratio) to receive either acupuncture or drug therapy. This study protocol was developed in accordance with the Standard Protocol Items: Recommendations for Intervention Trials (SPIRIT) [41]. This trial has been registered with the Chinese Clinical Trial Registry (ChiCTR). The flowchart of the trial design is shown in Figure 1.

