#### 2.4.1. Clinical Data Collection

All participants will be instructed to complete a headache diary every 4 weeks during the study. The headache diary will mainly record the time of migraine onset, migraine duration, migraine severity (detected by a visual analog scale), and use of rescue medicine.

The following clinical outcomes will be assessed by independent assessors who have been trained before participating in the study. The primary outcome is the change in frequency of migraine attacks, and the secondary outcomes include the changes in migraine days (days on which migraine attacks occurred), average migraine severity, gastrointestinal symptoms, psychiatric symptoms, and quality of life. The intensity and frequency of gastrointestinal symptoms will be assessed using the Gastrointestinal Symptom Rating Scale (GSRS) [42, 43]. As migraine is often accompanied by psychiatric symptoms, the Beck Anxiety Inventory (BAI) [44] and the Beck Depression Inventory (BDI) [45] will be used to measure the emotional states of migraineurs, and quality of life will be assessed using the Migraine-Specific Quality of Life Questionnaire (MSQ) [46].

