### 2.9. Statistical Analysis

#### 2.9.1. Clinical Data Analysis

The analysis plan will be determined before the study is conducted. Demographic characteristics, baseline characteristics, and clinical outcomes will be analyzed using SPSS25.0 statistical software based on the intention-to-treat population, which comprises subjects who receive, at least, one treatment and undergo, at least, one posttreatment efficacy evaluation. Missing data will be replaced by data from the last observation. Normally distributed continuous variables will be presented by means and standard deviations with 95% confidence intervals. Nonnormally distributed continuous variables will be described using medians and interquartile ranges. Categorical variables will be described using percentages and frequencies. The significance level used for statistical analysis with 2-tailed testing will be 5%. Qualitative data will be compared using the chi-square test. If the quantitative data are normally distributed, we will use analysis of variance to detect differences between the two groups; if not, the Mann–Whitney test will be used. Data sheets will be anonymized for data entry, and statistical analysis will be conducted by an independent statistician blinded to treatment allocation.

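### The 80% power is calculated for migraine days, a secondary outcome, and is not shown for the primary outcome, attack frequency

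*Protocol article*

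**What the plan says.** The abstract and section 2.4.1 of the protocol article agree on the primary outcome. Section 2.4.1 reads: "The primary outcome is the change in frequency of migraine attacks, and the secondary outcomes include the changes in migraine days". It describes migraine days as the days on which attacks occurred, so they are a separate quantity of lower rank.

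Section 2.5.1 contains the only power calculation. It takes its figures from an earlier comparison of the two treatments: "we anticipate that the change in the average number of migraine days in the acupuncture group will be 4.1 ± 3.5". The corresponding flunarizine figures are a mean of 1.9 and an SD of 2.3. With α = 0.05 and 1 − β = 0.80 it arrives at 30 per group, raised to 66 in total for 10% withdrawal. The section also mentions 12–27 individuals per group, but for the imaging and microbiota work.

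The article gives no mean, SD or effect size for attack frequency, and it does not say that migraine days stand in for it.

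**The concern.** A sample size calculation should show that the trial can answer its primary question. Here the endpoint that is powered is not the endpoint ranked first.

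The two measures are related but not interchangeable. On the article's own description, an attack that continues over two days is one attack and two migraine days. Section 2.3.1 also treats them as distinct, with a lower limit on attacks and a separate upper limit on migraine days. Their means, SDs and standardised differences may therefore differ. The introduction, citing the source of the planning figures together with one other study, credits acupuncture with fewer migraine days and makes no matching statement there about attack frequency.

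The first objective in section 2.1 is to re-evaluate efficacy, and the primary test carries it. If that test is null, the stated 80% cannot help a reader judge whether the trial could have detected a worthwhile difference. If migraine days are significant beside a null primary, the sample size section offers a ready argument for giving them more weight than their rank allows.

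**Working it through.** **Inputs**

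- Change in migraine days, acupuncture: 4.1, SD 3.5 (section 2.5.1)
- Change in migraine days, flunarizine: 1.9, SD 2.3 (section 2.5.1)
- α = 0.05 and power 0.80 (section 2.5.1); two-sided testing (section 2.9.1)
- Allocation 1:1 (section 2.2)
- Analysis of variance, which with two groups is equivalent to the t-test, or Mann–Whitney if the data are not normal (section 2.9.1)

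**Step 1. Reproduce the stated figure**

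- Difference = 4.1 − 1.9 = 2.2
- Pooled SD = √[(3.5² + 2.3²)/2] = √[(12.25 + 5.29)/2] = √8.77 = 2.961
- d = 2.2 / 2.961 = 0.743
- Normal approximation: n = 2(1.960 + 0.842)² / d² = 28.4, so 29 per group
- Noncentral t: n = 29.44, so 30 per group, with power 0.808 at 30

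The two-sided t-test gives the article's 30. A one-sided t-test would need only 24 and does not match. The stated number is therefore correct for migraine days. For the total, 60 × 1.10 = 66.

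**Step 2. What 30 per group offers for attack frequency**

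Solving the same two-sided t-test for the effect gives the smallest standardised difference with 80% power:

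- 30 per group: d = 0.736
- 33 per group (all 66 analysed): d = 0.700

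**Step 3. Power over a range of effects**

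The article gives no attack-frequency figure. The values of d below are assumptions on both sides of the planning effect; 0.743 is the migraine-days effect, included for reference.

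| d for attack frequency | Power, 30 per group | Power, 33 per group | n per group for 80% |
|---|---|---|---|
| 0.3 | 21% | 23% | 176 |
| 0.4 | 33% | 36% | 100 |
| 0.5 | 48% | 52% | 64 |
| 0.6 | 63% | 67% | 45 |
| 0.7 | 76% | 80% | 34 |
| 0.743 | 81% | 84% | 30 |
| 0.8 | 86% | 89% | 26 |

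The Mann–Whitney fallback changes little: under normality the requirement becomes 29.44 / (3/π) = 30.8, so 31 per group.

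**The case against.** The best case for the plan has four parts.

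- **The calculation is correct and the ranking is clear.** Both are true. The fault is a mismatch between the two, not a computing error.
- **The outcomes are close relatives from one headache diary, so their standardised effects may be similar.** That is possible, and an effect larger than 0.74 on attack frequency is no more excluded than a smaller one. It means one may not conclude that the trial is underpowered. It does not supply the missing justification, because the article neither makes this argument nor gives a figure for it.
- **More than 30 per group may be analysed.** Sixty-six are recruited, and section 2.9.1 carries the last observation forward for everyone with at least one treatment and one post-treatment evaluation. At 33 per group the detectable difference falls from 0.74 to 0.70 SD. The gain is modest and the question remains.
- **Two of the three objectives are mechanistic, and a null primary could still be read from its confidence interval.** Both points are fair. They soften the consequence, but efficacy is still the first objective and the stated power still belongs to another endpoint.

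It might also be said that a journal article condenses a fuller protocol. That would excuse missing detail. Here the article states a calculation, and it is for an outcome other than the one it names as primary.

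**Conclusion.** The concern holds. The 80% power in section 2.5.1 applies to the change in migraine days, and nothing in the article shows what power the trial has for its primary outcome. With 30 per group, 80% power for attack frequency requires a standardised difference of about 0.74 (0.70 if all 33 per group are analysed). Across assumed differences of 0.3 to 0.8 SD, power at 30 per group runs from 21% to 86%. These figures rest on a two-sided t-test at 5% with equal groups. They do not establish that the trial is too small, since the true attack-frequency effect is not given.

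**What to change.** At the least, keep attack frequency as primary and amend section 2.5.1 in three respects:

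- say that the 30 per group and the 80% power refer to the change in migraine days;
- give the detectable difference for attack frequency at 30 per group, about 0.74 SD, and convert it to attacks with a justified SD;
- give the power at the attack-frequency difference that the sponsor expects, with its source.

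This needs a change of wording and no extra patients. The power stated for the primary outcome may look less favourable.

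Two alternatives go further, and both are design choices for the sponsor:

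- **Make migraine days primary and attack frequency secondary.** This must be decided before any outcome data are seen. The abstract, section 2.4.1 and the registry entry would have to change to match section 2.5.1. Both measures come from the same diary, so data collection is unaffected.
- **Recalculate the sample size from a justified attack-frequency difference and SD.** The total may then change: 80% power would need 45 per group at d = 0.6 and 64 per group at d = 0.5, before withdrawal.

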#### 2.5.2. Randomization

To avoid possible selective bias, a statistician will use Statistical Product Service Solutions (SPSS) Statistics V25.0 to generate a table of random numbers that will be placed in opaque envelopes. This randomization scheme will be kept secure by a specially assigned person. The researchers will contact this designated person by telephone to acquire the corresponding random number and grouping for each participant enrolled in the study.

#### 2.5.3. Blinding

Owing to the difference between the two therapies, double-blind will be difficult to implement in this study. However, the purpose of blinding is to avoid the influence of subjective factors from the subjects and researchers on the study results. In order to minimize the subjective influence, we will ensure that evaluation and statistical analysis are carried out by a third party who is unaware of the grouping.

### 2.6. Intervention

The interventions will be implemented strictly in accordance with the Consolidated Standards of Reporting Trials (CONSORT) [51] and the Standards for Reporting Interventions in Clinical Trials of Acupuncture (STRICTA) [52].

#### 2.6.1. Acupuncture Group

In the acupuncture group, the needles will be placed at obligatory acupoints Fengchi (GB20), Shuaigu (GB8), and Baihui (DU20) in all treatments. Using syndrome differentiation, acupoints from other meridians will be chosen according to the location of headache as follows: Shaoyang headache: Waiguan (SJ5) and Yanglingquan (GB34); Taiyang headache: Kunlun (BL60) and Houxi (SI3); Yangming headache: Hegu (LI4) and Neiting (ST44); and Jueyin headache: Taichong (LR3) and Neiguan (PC6) (Table 2 and Figure 2). Except DU20, other acupoints will be selected bilaterally in this prescription. Acupoints other than the prescribed ones will not be used. The treatment strategy is based on experience from our previous study and consensus meetings with clinical experts [33]. Disposable sterile acupuncture needles (25 to 40 mm in length and 0.25 mm in diameter) will be used in the treatment. Each point will be needled to achieve the Deqi sensation, and needles will be retained for 30 minutes per session. Patients will receive 12 sessions of manual acupuncture treatment (once every other day to a total of three times per week, followed by a 2-day break) for a period of 4 weeks. Treatments will be performed by licensed acupuncturists who have received more than 3 years of training.

#### 2.6.2. Control Group

In the control group, flunarizine (manufacturer: Chongqing Kerui Pharmaceutical Co., LTD., Chongqing, China; SFDA approval number: H19994054) will be administered at a dose of 5 mg daily, following migraine guidelines and the professional advice of neurologists [22–25]. Patients will take the capsules continuously for 4 weeks without interruption.

In principle, participants should not take any analgesic medication during the study period. However, ibuprofen sustained-release capsule (Manufacturer: Tianjin Smith Kline & French laboratories, LTD., Tianjin, China; SFDA approval number: H20013062) can be taken as a rescue medicine for unbearable headaches, but the usage must be recorded in the headache diary.

### 2.7. Data Management and Quality Control

To ensure successful study implementation, all researchers will receive standardized training before the research starts. Clinical data will be recorded and managed by two trained graduate students using paper and electronic case report forms (CRFs). To avoid data entry errors, data will be proofread by two independent researchers when entering the electronic CRFs. All study data will be entrusted to the Brightech-Magnasoft Clinical Information Management System (CIMS) (address: [name], [contact], website: http://www.brightech-intl.com) for data management and analysis. MRI and gut microbiota data will be collected strictly in accordance with the operating procedures and trial design.

### 2.8. Safety and Monitoring

During the study, patients receiving acupuncture or flunarizine treatment may experience adverse events, such as pain, fainting, bleeding, hematoma, infection (acupuncture treatment), drowsiness, and fatigue (flunarizine treatment). Regardless of whether the adverse events are related to the treatment in this study, they will be recorded in detail and handled properly. Serious adverse events will be immediately reported to the primary investigator to assess whether to proceed with the study.

### 2.9. Statistical Analysis

#### 2.9.1. Clinical Data Analysis

The analysis plan will be determined before the study is conducted. Demographic characteristics, baseline characteristics, and clinical outcomes will be analyzed using SPSS25.0 statistical software based on the intention-to-treat population, which comprises subjects who receive, at least, one treatment and undergo, at least, one posttreatment efficacy evaluation. Missing data will be replaced by data from the last observation. Normally distributed continuous variables will be presented by means and standard deviations with 95% confidence intervals. Nonnormally distributed continuous variables will be described using medians and interquartile ranges. Categorical variables will be described using percentages and frequencies. The significance level used for statistical analysis with 2-tailed testing will be 5%. Qualitative data will be compared using the chi-square test. If the quantitative data are normally distributed, we will use analysis of variance to detect differences between the two groups; if not, the Mann–Whitney test will be used. Data sheets will be anonymized for data entry, and statistical analysis will be conducted by an independent statistician blinded to treatment allocation.

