### 2.4. Data Collection

At the 4-week baseline, patient demographic surveys (age, sex, height, weight, education, disease course, and medical history) will be administered. Clinical outcomes, fecal samples, and magnetic resonance imaging (MRI) data will be collected at the 4-week baseline, end of the 4-week intervention, and at the 12-week follow-up (Table 1).

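### Last observation carried forward, the only missing-data rule, can bias the week-16 comparison because it fills scale scores with end-of-treatment values 12 weeks after treatment stopped

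*Protocol article*

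**What the plan says.** Section 2.9.1 of the protocol article states the rule in one sentence, "Missing data will be replaced by data from the last observation", with no alternative method and no sensitivity analysis. It applies to an analysis set described as intention-to-treat but limited to "subjects who receive, at least, one treatment and undergo, at least, one posttreatment efficacy evaluation".

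The schedule is as follows.

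- **Treatment:** the Abstract says "Participants in both groups will receive treatment for a period of 4 weeks".
- **Clinical outcomes:** section 2.4 places collection at baseline, "end of the 4-week intervention, and at the 12-week follow-up". Table 1 puts that last visit at week 16.
- **Scales:** Table 1 marks the visual analog scale, GSRS, BAI, BDI and MSQ at weeks 0, 4 and 16 only.
- **Diary:** section 2.4.1 says "All participants will be instructed to complete a headache diary every 4 weeks during the study".
- **Primary outcome:** "The primary outcome is the change in frequency of migraine attacks", with no time point attached.
- **Withdrawal:** section 2.5.1 allows for 10%, giving 66 patients in total.

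**The concern.** Carrying the last value forward assumes that nothing changes after a patient is last seen. Here the last scale value before a missing week-16 visit is the one taken as treatment ends, and the value being filled lies 12 weeks off treatment. If benefit fades once needling or capsules stop, the patients who were lost keep a benefit that the patients who stayed have partly given up.

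The two arms need not cancel. The treatments cannot be double-blinded (section 2.5.3), one arm attends 12 sessions while the other takes daily capsules (section 2.6), and the expected adverse events differ (section 2.8). Dropout could therefore differ by arm, and so could the course after treatment. At stake is whether a week-16 difference between arms reflects the treatments or who was lost.

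**Working it through.** **Planning figures.** Section 2.5.1 uses changes in migraine days of 4.1 (SD 3.5) and 1.9 (SD 2.3). The difference is 2.2, the pooled SD is √((3.5² + 2.3²)/2) = 2.96 and d = 2.2/2.96 = 0.743. With two-sided α = 0.05 and 80% power, the noncentral t gives 30 per group (power 0.808), as stated. Then 60 × 1.1 = 66, or 33 per arm. The only missingness figure in the article is the 10% behind that step, about 3 patients per arm.

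**Bias formula.** In one arm let p be the share missing at week 16, D the mean improvement lost between the carried observation and week 16, and μ the true week-16 mean improvement. If missingness is unrelated to outcome within the arm, the filled-in mean is

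(1 − p)μ + p(μ + D) = μ + pD.

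The bias in the difference (acupuncture minus flunarizine) is therefore p_A·D_A − p_F·D_F. It favours the arm with the larger product.

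**Applied to the planning difference of 2.2 migraine days.** The article gives neither p by arm nor D, so both are assumed. The carried value is taken to be week 4, which is the longest carry possible for a diary outcome.

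| Missing (A / F) | Improvement lost (A / F), days | Bias, days |
|---|---|---|
| any | 0 / 0 | 0 |
| 10% / 10% | 2.05 / 0.95 (half in each arm) | 0.205 − 0.095 = +0.11 |
| 10% / 10% | 4.1 / 1.9 (all in each arm) | 0.41 − 0.19 = +0.22 |
| 10% / 10% | 4.1 / 0 | +0.41 |
| 10% / 10% | 0 / 1.9 | −0.19 |
| 20% / 5% | 2.05 / 2.05 | 0.15 × 2.05 = +0.31 |
| 5% / 20% | 2.05 / 2.05 | −0.31 |
| 20% / 0% | 4.1 / any | +0.82 |

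**Applied to attacks.** Assume SD 2.5, week-4 to week-16 correlation 0.6, 33 per arm, the same rebound in both arms, no true week-16 difference, and 5% versus 20% missing.

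- Rebound of 1 attack: 1 × (0.20 − 0.05) = 0.15 attacks.
- Rebound of 2 attacks: 2 × 0.15 = 0.30 attacks.
- The standard error is about 2.5 × √(2/33) = 0.615, so these are about 0.24 and 0.49 standard errors.
- In 20,000 simulated trials the nominal 5% t-test rejected in about 5.6% and 7.5%. With equal dropout it rejected in 5.0%.

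**Standard error.** In the same set-up with 10% missing per arm, the mean reported standard error was 0.613 to 0.631 for rebounds of 0 to 2 attacks. The sampling SD of the carried-forward estimate was 0.617 to 0.628. The two agree.

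**Alternative method.** With the protocol's SDs and correlations of 0.3 to 0.7, a likelihood-type regression estimator that uses week-4 data had bias of about 0.01 day or less in every scenario run. In all of these, missingness was unrelated to outcome within arm.

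**The case against.** Four points can be made for the plan, and most of each stands.

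1. **The primary outcome comes from the diary.** With diaries every 4 weeks, a patient lost late in follow-up may have off-treatment records after week 4, and the rule would carry the latest of them. A reader might infer from Table 1 that attack frequency is also carried across 12 weeks. The article does not establish that. The full 12-week carry is clear only for the scales, and even average severity is also recorded in the diary.

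2. **Baseline will seldom be carried forward.** One might suppose that early dropouts get their baseline value. The analysis set requires a post-treatment evaluation, which largely excludes them. This is mainly a week-16 matter.

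3. **Bias is conditional.** It needs drift off treatment and unequal products of share missing and drift. The article reports neither. With the same rebound and the same dropout in both arms it is zero. No primary time point is given, so if week 4 is primary the main comparison is hardly touched.

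4. **Precision.** Because filled-in values are counted as observed, a reader might infer that standard errors are about 5% too small, from √(30/33) = 0.95. That ratio treats a carried value as carrying no information. The simulation shows the reported error matching the actual spread of the carried-forward estimate at 10% missing, so the inference is not supported.

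None of this supports carry-forward as the sole method. The intermediate diaries count against it: a repeated-measures model would use every window, whereas the rule keeps only the last.

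**Conclusion.** The concern holds in a limited form. The protocol fixes last observation carried forward as its only handling of missing clinical data. For the scales, that means an end-of-treatment value standing in for a week-16 value 12 weeks after treatment stopped. This can bias the week-16 comparison towards either arm, and the direction cannot be told from the article.

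The size depends on assumptions. At 10% missing per arm it is about 0.1 to 0.2 day on a planned 2.2-day difference if both arms lose the same half or all of their benefit, and up to 0.41 day if only the acupuncture arm loses its benefit. At 5% versus 20% missing with equal rebounds of 1 or 2 attacks it is about 0.15 or 0.30 attacks, with type I error near 5.6% or 7.5%. It is zero with no drift or equal products. The documents do not support saying that the comparison will be biased, that the primary outcome is carried over the full 12 weeks, or that the standard errors are materially understated. The change is worth making because it is cheap, not because the planned rate implies a large error.

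**What to change.** In section 2.9.1, replace carry-forward as the main method with one of these:

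- a likelihood-based repeated-measures model on baseline, week 4, any intermediate diary windows and week 16, with arm, time and arm-by-time terms (a mixed model for the scales and migraine days, a count model for attacks); or
- multiple imputation under missing at random, using the same earlier measurements.

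Last observation carried forward can stay, at most, as a sensitivity analysis.

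The cost is a wording change and a little more analysis work. It needs no new visits, patients or measurements, and the named package, SPSS 25, supports both mixed models and multiple imputation. The price is reliance on missing at random, which the data cannot confirm. It is nonetheless a weaker demand than assuming no change after treatment stops.

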#### 2.3.1. Inclusion Criteria

Eligible participants must meet the following criteria: (1) men or women aged 18–55 years; (2) right handed, length of education ≥6 years; (3) a history of migraine of, at least, 1 year with the first onset before the age of 50 years; (4) migraine attacks ≥2 times and number of migraine days <15 days per month during the past 3 months and baseline observation; (5) completion of the baseline headache diary; and (6) provision of written informed consent.

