#### 2.9.4. Tripartite Network Analysis

A tripartite network analysis based on graph theory will be used to compare the interactions among brain network activity, gut microbiota, and clinical data for migraineurs in the acupuncture and flunarizine groups. The interactions between the phenome (clinical symptoms), gut microbiome (fecal microbial community), and connectome (indices of regional centrality in the brain) will be analyzed using Spearman's correlations in MATLAB R2015b. Fisher's *r*-to-*z* transformation will be used to measure the correlation coefficient difference between the acupuncture and flunarizine group. The *Z* test will be applied, and an uncorrected value of *p* < 0.05 will be considered statistically significant. The software Cytoscape 3.7.2 (https://cytoscape.org) will be used to visualize and generate a brain activity, gut microbiota community, and clinical data interaction network. This association of this network will be included if Pearson's correlation for the data of the different groups achieves significance. The architecture of different group networks will be based on a significantly different network. The results will be described in terms of direct (correlations with microbial community) and indirect effects (clinical symptoms and brain connectivity metric) with an emphasis on the interaction between microbiome and clinical symptoms. An independent sample *t*-test will be used to examine between-group differences in clinical variables.

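### Clinical change scores are compared without baseline as a covariate and with a test chosen by observed normality: a valid analysis that gives up precision and leaves the reported effect measure open

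*Protocol article*

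**What the plan says.** Section 2.4.1 defines the main endpoint: "The primary outcome is the change in frequency of migraine attacks". Section 2.9.1 then sets a single rule for quantitative clinical data. When they are normally distributed, "we will use analysis of variance to detect differences between the two groups"; "if not, the Mann–Whitney test will be used". No covariate appears, no criterion for normality is given, and no separate rule is set for the primary outcome. Testing is two-sided at 5%.

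The baseline measurement exists for everyone. Section 2.3.1 lists "completion of the baseline headache diary" among the inclusion criteria, and Table 1 schedules the diary from week −4. The same section limits the baseline range: "migraine attacks ≥2 times and number of migraine days <15 days per month during the past 3 months and baseline observation".

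Section 2.9.4, on the tripartite network, adds that an independent-sample t-test "will be used to examine between-group differences in clinical variables".

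**The concern.** In a trial of about 30 per arm, a baseline value measured on every participant is the cheapest source of precision. A change score uses that value in a fixed way, by subtracting it with a coefficient of one. Unless that happens to be the best coefficient, the difference in mean change carries avoidable noise, and chance imbalance in baseline attack frequency passes into the estimate through regression to the mean. A regression on baseline estimates the coefficient instead.

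The second matter is the switch between tests. Analysis of variance estimates a difference in mean change; Mann–Whitney compares ranks. If the observed distribution decides between them, the trial does not know in advance which effect measure it will report for its primary outcome, and the protocol gives no criterion that would let a reader check the choice.

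**Working it through.** **1. Reproducing the plan's figure.** Section 2.5.1 assumes that "the change in the average number of migraine days in the acupuncture group will be 4.1 ± 3.5", against 1.9 ± 2.3 with flunarizine, with α = 0.05 and power 0.80.

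- Difference: 4.1 − 1.9 = 2.2.
- Pooled SD: √((3.5² + 2.3²)/2) = √8.77 = 2.961.
- Standardised effect: 2.2/2.961 = 0.743.
- A two-sided, unadjusted two-sample t-test (noncentral t) needs 30 per arm, with power 80.8%.

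The stated 30 is therefore the size for an unadjusted comparison of change scores.

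**2. Effect of adjusting for baseline.** Let baseline and follow-up have a common variance σ² and correlation ρ.

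- Change score: 2σ²(1−ρ).
- Follow-up adjusted for baseline: σ²(1−ρ²).
- Ratio, adjusted to change: (1+ρ)/2.

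The protocol gives no ρ, so it is an assumption shown as a range. The SD of change is held at 2.961 and one further degree of freedom is spent on the covariate.

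| ρ (assumed) | Variance ratio | Residual SD | Standardised effect | n per arm for 80% | Power at 30 per arm |
|---|---|---|---|---|---|
| unadjusted | 1 | 2.961 | 0.743 | 30 | 80.8% |
| 0.3 | 0.65 | 2.388 | 0.921 | 20 | 93.9% |
| 0.5 | 0.75 | 2.565 | 0.858 | 23 | 90.4% |
| 0.7 | 0.85 | 2.730 | 0.806 | 26 | 86.6% |
| 0.8 | 0.90 | 2.809 | 0.783 | 27 | 84.6% |

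The direction does not depend on equal variances. With baseline SD σ₀ and follow-up SD σ₁, the change-score variance minus the adjusted variance is σ₀² + σ₁² − 2ρσ₀σ₁ − σ₁²(1−ρ²) = (σ₀ − ρσ₁)², which is never negative.

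**3. Effect of the normality switch.** The protocol names no criterion, so a Shapiro–Wilk test at 5% in each arm was assumed, with 30 per arm, SDs of 3.5 and 2.3, and 6,000 simulated trials.

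| Distribution of change | Mann–Whitney chosen | Rejection under equal means: t-test | Rejection under equal means: two-stage rule | Power at difference 2.2: t-test | Power at difference 2.2: two-stage rule |
|---|---|---|---|---|---|
| Normal | about 10% | 5.2% | 5.3% | 80.6% | 80.5% |
| Skewed (shifted gamma, shape 2) | about 94% | 5.7% | 9.8% | 82.8% | 82.1% |

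The 9.8% arises because the arms have equal means but different spreads and skewed shapes, so the rank hypothesis is false while the mean hypothesis is true. It shows that the two branches answer different questions.

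In simulations of attack counts (gamma-Poisson, entry at 2 or more attacks, baseline rate 3 to 8, gamma shape 1.5 to 8, all assumed), the two-stage rule rejected in about 5% of trials when the arms shared one distribution. Its power stayed within about 2 percentage points of the plain t-test in all nine settings, while baseline adjustment had higher power. The gain thus comes from the covariate and not from fixing the choice of test.

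**The case against.** The best defence is that nothing here is an error. A comparison of change scores is unbiased under randomisation, the sample size was calculated for that comparison, and on its own inputs it has the power claimed. The article is also condensed: Section 2.9.1 says the analysis plan is settled before the study begins, and an unseen plan may hold the normality criterion and the covariates. The first part stands in full. The second stands for the missing criterion, but the unadjusted two-branch rule is stated in the article, so proposing a better rule does not rest on an omission.

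A reader might infer stronger points that the document does not support.

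- *Baseline is ignored.* It is not. The primary outcome is a change, so baseline enters by subtraction; it is only not a covariate.
- *Section 2.9.4 introduces a third competing test.* With two groups, one-way analysis of variance and the equal-variance t-test are the same test (F = t²). The only discrepancy is that Section 2.9.4 does not repeat the Mann–Whitney fallback, and it concerns the network analysis.
- *The choice of branch is a coin toss.* The document gives no mean, SD or dispersion for attack frequency. In the count simulations the parametric branch was chosen in 23% to 73% of runs, depending on the assumed inputs.
- *Letting the data choose the test inflates the false-positive rate or costs power.* When the arms share one distribution it does little of either. The inflation in the working needs skewed changes with unequal spread.

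**Conclusion.** This is a free improvement, not the correction of a mistake. The planned analysis is valid and delivers 80.8% power on the protocol's inputs. Adjusting for the baseline diary count would cut the variance of the effect by 10% to 35% for ρ from 0.8 down to 0.3, raising power at 30 per arm to between 84.6% and 93.9%. Equivalently, the unadjusted analysis needs 11% to 54% more patients for the same precision (1/0.90 to 1/0.65).

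These sizes rest on three assumptions: the value of ρ, equal baseline and follow-up variances, and the transfer to attack frequency of inputs that Section 2.5.1 gives for migraine days. The normality switch is the smaller matter. Its main consequence is that the primary effect measure is not fixed in advance.

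**What to change.** In Section 2.9.1, prespecify one primary model: the 4-week attack count regressed on arm with the baseline 4-week count as covariate. Either ANCOVA with robust standard errors, reported as an adjusted difference, or negative binomial regression with log baseline count, reported as a rate ratio, would serve. Choose one in advance and give the 95% confidence interval.

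Use baseline-adjusted models for the other quantitative clinical outcomes (migraine days, severity, GSRS, BAI, BDI, MSQ). Keep Mann–Whitney as a sensitivity analysis that does not depend on a normality check. Align the t-test sentence in Section 2.9.4 with the same model. If the full analysis plan already does this, the article's wording only needs to be brought into line.

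The cost is a change of wording before the data are analysed. The baseline diary is already required, and neither the sample size nor the visit schedule changes.
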